The TOROS project consists of a randomized controlled trial (RCT), and a supplementary case–control study. The primary objective of the RCT is to evaluate whether CPAP treatment improves cognitive and functional outcomes in stroke patients with OSA (AHI ≥ 15), as assessed by a neuropsychological test battery and by measures of neurological status and functional dependence. The aim of the supplementary case–control study is to explore the association between OSA and cognitive and functional status in stroke patients. Our hypothesis is that stroke patients with OSA have a poorer functional status and greater cognitive impairment compared to stroke patients without OSA. In both the RCT and the case–control study the secondary objectives are: 1) to evaluate the effects of OSA (and its treatment) on sleep quality, fatigue and mood; and 2) to evaluate the long-term effects of OSA on societal participation.

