## Methods

### Design

In the RCT, 70 OSA patients will be randomized to receive four weeks of CPAP treatment or four weeks of TAU. Patients randomized to TAU will start with CPAP treatment after the four-week intervention period. Neuropsychological assessment and examination of functional status, the primary outcome measures, are conducted at baseline and repeated after the four-week intervention period and at two-month follow-up. The secondary measures sleep quality, fatigue, and mood are assessed at the same time points as the primary outcome measures. To ascertain whether OSA improves with CPAP treatment, direct measurements of OSA, including AHI and level of oxygen desaturation during sleep, are made at baseline, at the end of the intervention period, and at two-month follow-up. To assess treatment compliance, the CPAP device registers CPAP usage per night, the air pressure and the residual AHI. At four weeks, and three, six and twelve months after enrollment the rehabilitation physician checks the compliance.

To test the hypothesis of the case–control study that OSA is associated with poor functional status and greater cognitive impairment, 70 stroke patients diagnosed with OSA are compared to 70 stroke patients without OSA on the primary and secondary outcomes at admission to the rehabilitation unit (baseline).

In a subgroup of the stroke patients without OSA (N = 35) the assessment of primary and secondary outcome measures will be repeated after four weeks and three months. The outcomes will be compared to the recovery of OSA patients.

All patients included in the TOROS study are asked to fill out a questionnaire on participation in work, leisure and social activities at six months and one year after inclusion. The study design is illustrated in Figure 1.

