### Statistical analyses

All statistical analyses will be performed with SPSS 19 (IBM; Armonck, USA) or later versions of this package. Depending on the level of measurement, parametric statistics (Student’s *t*-test and analysis of (co)variance) or non-parametric statistics (*χ*^2^ and Fisher’s exact test) will be used. Statistical significance will be set at a p-value of 0.05 or less. Socio-demographic and clinical characteristics at baseline will be presented using descriptive statistics. If group differences are observed at baseline on one or more background variables, those variables will be included as covariates in all further analyses.

For the RCT, the therapy effects on the primary and secondary outcome measures will be examined using a two factor (group × time) multivariate analysis of variance (MANOVA). Effect sizes will be calculated for all analyses using standard statistical procedures. To control for the multiple comparisons of cognition and functional status, two separate MANOVA’s will be performed. Given that we have two primary outcomes defined for the study (i.e., cognitive and functional outcomes), we will subsequently follow Hochberg’s step-up procedure [36] to control the false discovery rate.

Data will be analyzed according to the intention-to-treat principle. Additionally, a per-protocol analysis will be performed. Depending on the variability of compliance, a secondary analysis of good versus poor compliance will be conducted. In an exploratory analysis, we will investigate whether the effectiveness of CPAP therapy varies as a function of clinical diagnosis, level of cognitive functioning, and demographic background.

For the supplementary case–control part of the study, OSA patients will be compared with the control group of non-OSA patients on primary and secondary outcome measures using a MANOVA. As with the RCT, a separate analysis will be performed for cognition and functional status, and the Hochberg’s step-up procedure will be followed. For the follow-up of the USER-P questionnaire, within group changes will be assessed using paired t-tests and between group comparison will be made with two sample *t*-test.

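### The group × time test of therapy effects is not tied to week 4, so it does not isolate CPAP versus TAU from early versus delayed CPAP

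*Protocol article*

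**What the plan says.** All references are to the protocol article.

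- **Design, treatment:** "70 OSA patients will be randomized to receive four weeks of CPAP treatment or four weeks of TAU". Then: "Patients randomized to TAU will start with CPAP treatment after the four-week intervention period".
- **Design, visits:** the primary outcome assessments "are conducted at baseline and repeated after the four-week intervention period and at two-month follow-up". The secondary measures of sleep quality, fatigue and mood "are assessed at the same time points as the primary outcome measures".
- **Statistical analyses:** the "therapy effects on the primary and secondary outcome measures will be examined using a two factor (group × time) multivariate analysis of variance (MANOVA". One MANOVA is planned for cognition and one for functional status. No other test of the primary outcomes in the RCT is named, and the section does not say which visits make up the time factor.
- **Statistical analyses, analysis set:** "Data will be analyzed according to the intention-to-treat principle".
- **Background, objectives:** a secondary objective of both the RCT and the case–control study is "to evaluate the long-term effects of OSA on societal participation". Participation is measured at six months and one year.

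**The concern.** The randomised contrast of CPAP with TAU exists only up to the week-4 visit. After that, patients in the TAU arm also start CPAP. Under intention-to-treat they are still analysed as TAU, so the two-month visit compares CPAP started early with CPAP started about four weeks later.

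If time has the three scheduled levels, group × time is an omnibus test with 2 degrees of freedom per outcome and no direction. It rejects when the arms diverge at week 4, at follow-up, or at both, and it does not say which. The objective is whether CPAP improves outcome, and the Discussion describes the comparison as CPAP against TAU. Only the week-4 contrast answers that. What is at stake is what the primary p-value means: an interaction driven by the follow-up visit would be reported as a therapy effect.

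**Working it through.** **Inputs from the article.** Target 70 patients (35 per arm). Planned cognitive effect 0.75 SD, 80% power, at least 28 per arm. Visits and crossover as above.

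**Assumed, because the article gives no values.** SD 1 at each visit; equal correlation ρ between visits of 0.5, 0.6 or 0.7; complete data; one outcome standing in for the multi-domain MANOVA.

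**The plan's own figure.** Normal approximation, n per arm = 2(z₁₋α/₂ + z₀.₈)² / d² = 2(1.960 + 0.842)² / 0.75² = 27.9, so 28. The stated 28 per arm is therefore a two-sided 0.05 calculation for a single between-arm difference. A one-tailed 0.05 would give 22. Two-sided 0.05 is used below.

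**Formulas.** Let δ be the between-arm differences at (baseline, week 4, follow-up) and n = 35, so n/2 = 17.5. Power comes from the noncentral F distribution with noncentrality λ.

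- Two-visit group × time (baseline, week 4): λ = 17.5 d² / [2(1 − ρ)], on 1 and 68 df.
- Three-visit group × time: λ = 17.5 Σ(δᵢ − δ̄)² / (1 − ρ), on 2 and 67 df.
- Week-4 ANCOVA with baseline as covariate: λ = 17.5 d² / (1 − ρ²), on 1 and 67 df.

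**Check 1: no week-4 difference, 0.5 SD at follow-up only.** δ = (0, 0, 0.5), so Σ(δᵢ − δ̄)² = 0.25 − 0.25/3 = 0.1667. At ρ = 0.5, λ = 17.5 × 0.1667 / 0.5 = 5.83.

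| ρ | Three-visit test rejects | Test using baseline and week 4 only |
|---|---|---|
| 0.5 | 55.1% | 5% |
| 0.6 | 65.4% | 5% |
| 0.7 | 78.5% | 5% |

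The sign of the follow-up difference makes no change to these figures.

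**Check 2: planned week-4 effect of 0.75 SD.** At ρ = 0.5:

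- Two-visit: λ = 17.5 × 0.5625 / 1 = 9.84.
- Three-visit, half the difference left at follow-up: δ = (0, 0.75, 0.375), sum of squares 0.28125, λ = 17.5 × 0.28125 / 0.5 = 9.84.
- Three-visit, none or all left: sum of squares 0.375, λ = 13.1.
- ANCOVA: λ = 17.5 × 0.5625 / 0.75 = 13.1.

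| ρ | Week-4 ANCOVA | Two-visit | Three-visit, none or all left | Three-visit, half left |
|---|---|---|---|---|
| 0.5 | 94.6% | 87.1% | 89.7% | 79.0% |
| 0.6 | 97.2% | 93.3% | 95.3% | 87.6% |
| 0.7 | 99.1% | 97.9% | 98.9% | 95.3% |

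With half the difference left, λ equals that of the two-visit test, and the loss is the price of the extra degree of freedom: 8.1 points at ρ = 0.5 and 2.6 at ρ = 0.7. With none or all left, adding the visit gains 1.0 to 2.6 points. The remaining gap to ANCOVA (7.5 points at ρ = 0.5, 1.2 at ρ = 0.7) comes from how baseline is used, not from the follow-up visit.

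**The case against.** The strongest reply is that the three-visit test is inferred. The statistical section does not list the time levels, the Design describes the randomised comparison as four weeks against four weeks, and a condensed article may leave contrasts to a fuller plan. It is right that this is an inference. But the article does state its test and its visits, and nothing limits that test to week 4. If two visits were meant, one clause would settle it.

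A reader might go further than the documents allow in four ways.

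- **That the primary test is not a test of CPAP versus TAU at all.** The week-4 contrast is one of the two interaction contrasts. If CPAP has no effect at any time, the interaction is null and type I error stays at 5%.
- **That 55% to 78% is a false-positive rate.** A follow-up difference between randomised arms is a real effect of early versus delayed CPAP. The error would lie in labelling it as the four-week therapy effect.
- **That pooling generally hides a week-4 benefit.** At the planned effect, power falls only under partial catch-up. Treating baseline as a repeated measure is valid under randomisation; ANCOVA is more efficient, which is a separate matter.
- **That participation at six and twelve months can show nothing about OSA.** The article places that analysis in its case–control paragraph, and the comparison still describes OSA and non-OSA patients under the care given. Treatment may attenuate the difference, so the objective's wording is loose rather than unanswerable.

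**Conclusion.** The point holds as one of attribution, not validity. On the natural reading of the Design and Statistical analyses sections, the primary test does not isolate CPAP versus TAU, and a significant result could come from the period in which both arms have started CPAP. With 35 per arm and ρ from 0.5 to 0.7, a 0.5 SD difference confined to follow-up is enough for rejection in about 55% to 78% of trials.

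Power is the lesser issue. For 0.75 SD at week 4 with half the difference left at follow-up, the three-visit test has 79% to 95% power, against 87% to 98% for the two-visit version and 95% to 99% for week-4 ANCOVA. These figures rest on the assumed correlations, effect patterns and single outcome; the interpretive problem does not depend on them.

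**What to change.** In Statistical analyses, define the primary therapy effect as the between-arm difference at the four-week assessment, adjusted for the baseline score (ANCOVA, or MANCOVA across domains). Analyse the two-month visit separately and label it as early versus delayed CPAP.

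As a separate minor change, describe the six- and twelve-month participation comparison as OSA patients offered CPAP versus non-OSA patients.

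The cost is wording only: the week-4 and baseline data are already scheduled, and no patients or visits are added. The downside is that the two-month visit leaves the primary test and becomes secondary. The change should be made before analysis, because it decides what the primary p-value refers to.

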### Patient sample and procedures

This study is conducted in Heliomare rehabilitation center in the Netherlands. Annually, approximately 150 stroke patients are admitted to Heliomare. Neurologists or rehabilitation physicians of hospitals in the surrounding area refer patients. Patients with vascular dementia or comorbid neurodegenerative diseases (e.g., Alzheimer’s or Parkinson’s disease) are excluded from rehabilitation in Heliomare and are referred to the rehabilitation unit of a nursing home. The majority of the admitted patients are in the post-acute phase, i.e., on average, two to three weeks post-stroke. The average length of stay in Heliomare is nine weeks (standard deviation of four weeks). An earlier study showed that the prevalence of OSA in stroke patients admitted to Heliomare is around 50% [23]. At admission to the rehabilitation unit, stroke severity and functional dependence scales are used to determine the patient’s functional status. In the first week of hospitalization, patients are interviewed with a questionnaire to determine the presence of common symptoms of OSA. Subsequently, their oxygen desaturation index (ODI), defined as the mean number of desaturations of ≥3% from baseline per hour, is assessed with nocturnal pulse oximetry. Patients with an ODI of five or higher are further tested for OSA by polygraphy. Patients with an AHI of 15 or higher on polygraphy are diagnosed with OSA and patients with a normal ODI (<5) [23,24] or AHI below 15 are defined as non-OSA patients. Within four weeks of admission, a neuropsychological assessment is administered to determine the level of cognitive functioning. Stroke patients meeting the following inclusion criteria are invited to participate within six weeks from admission to Heliomare: [1] stroke confirmed by a neurologist, [2] age between 18 and 85 years, [3] admission to Heliomare between 1 and 16 weeks post-stroke, and [4] able to participate in the OSA screening and neuropsychological assessment. Exclusion criteria are: [1] severe unstable medical conditions, respiratory failure or history of severe congestive heart failure, [2] traumatic brain injury, [3] severe aphasia, confusion or psychiatric comorbidity, [4] central sleep apnea or previously diagnosed OSA. Patients with severe OSA (AHI >60 and oxygen desaturations below 70%), which could endanger the patient’s health if treatment is not immediately started, are excluded from the RCT part of the study. Before inclusion, patients give written informed consent.

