### Primary outcomes

The primary outcome measures of this study are cognition and functional status. The following nine cognition domains are assessed: vigilance, attention, memory, working memory, executive functioning, language, visuoperception, psychomotor ability and intelligence. The neuropsychological test battery of standardized neuropsychological tests [26] is assessed by a trained psychological assistant. For a number of cognitive domains, non-verbal alternative tests are included for patients with aphasia. A language comprehension test is also included for aphasic patients. The obtained test scores are transformed into demographically corrected z-scores. In case of multiple tests within one domain, the average z-score for the domain is calculated. In Table 1 all tests are summarized by cognitive domain.

**Table 1 T1:** Neuropsychological tests by cognitive domain

** *Cognitive domain* **	** *Neuropsychological test* **
Vigilance	Psychomotor vigilance task
Attention	D-Kefs trail making test (TMT)
	*Color trails test
	d2 Test of attention
Memory	Rey’s auditory verbal learning test
	*Location learning test
Working Memory	WAIS-III letter-number sequencing
	*WMS-IV symbol span
Executive functioning	D-Kefs TMT letter-number switching
	Tower of London
Language	GIT-II category fluency
	**Token test
Visuoperception	D-Kefs TMT visual scanning
	Bells test
Psychomotor ability	D-Kefs TMT motor speed
	Finger tapping
Intelligence	WAIS-III matrix reasoning

*non-verbal alternative; **only administered in patients with aphasia.

Functional status is assessed by measures of neurological status and functional dependence. The rehabilitation physician administers two scales of neurological status, the Canadian Neurological Scale [27] and the National Institutes of Health Stroke Scale [28]. The obtained scores are transformed into z-scores and averaged into one score for neurological status. The nurse practitioner scores the level of functional dependence on the Utrecht Scale for Evaluation of Rehabilitation [29]. This scale can be converted to the Barthel Index [30].

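### As written, the nine-domain cognitive MANOVA is a complete-case analysis, which fits poorly with the stated intention-to-treat principle and a sample size without dropout allowance

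*Protocol article*

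**What the plan says.** The Primary outcomes section defines cognition by nine scores: "The following nine cognition domains are assessed: vigilance, attention, memory, working memory, executive functioning, language, visuoperception, psychomotor ability and intelligence". Where a domain has several tests, their z-scores are averaged. Some domains have non-verbal alternatives for patients with aphasia.

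The Design section places the primary assessments at baseline, after the four-week intervention and at two-month follow-up. It also says that the control arm starts CPAP once the four weeks are over.

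Under Statistical analyses, the therapy effects "will be examined using a two factor (group × time) multivariate analysis of variance (MANOVA"). Cognition and function are kept apart: "To control for the multiple comparisons of cognition and functional status, two separate MANOVA’s will be performed". The software is fixed too: "All statistical analyses will be performed with SPSS 19 (IBM; Armonck, USA) or later versions of this package". The same section then states the analysis principle: "Data will be analyzed according to the intention-to-treat principle". It does not list the levels of the time factor and names no imputation.

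The Sample size section derives a cognitive minimum of 56 patients and raises it to 70. It attributes the increase to CPAP compliance and does not mention dropout.

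**The concern.** A classical repeated-measures MANOVA works on each patient's full outcome vector. A patient with one empty cell in that vector does not enter the test. This is a property of the method; the article does not state it. With nine domains the vector is long: 27 scores over three visits, or 18 over two. Patients lost this way are analysed in neither arm.

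The article gives reasons to expect some gaps:
- Patients with non-severe aphasia are eligible, and only some domains have an alternative test.
- Table 1 gives vigilance and intelligence one test each, so one missed test empties the domain.
- Patients may be invited up to six weeks after admission, while the mean stay is nine weeks (SD four). The Intervention section foresees discharge during the four weeks.

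Two things are at stake. If completeness is related to impairment or to tolerance of CPAP, the comparison no longer has the protection of randomization. And the analysed number can fall below the minimum that the plan set for itself.

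**Working it through.** **Inputs from the article.** Nine domains; assessments at baseline, week 4 and follow-up; target of 70 (35 per arm); cognitive effect 0.75 SD, 80% power, minimum 56 (28 per arm).

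**Assumed inputs.** The missing rates, because the article gives none.

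**1. The plan's own figure.** Patients per arm = 2(z₀.₉₇₅ + z₀.₈₀)² / 0.75² = 2(1.960 + 0.842)² / 0.5625 = 27.9, so 28 per arm and 56 in all. This reproduces the stated minimum with a two-sided 5% test. (A one-tailed 5% test would give 22 per arm, or 44.) The target equals 56 / 0.80 = 70. Since the article assigns that increase to compliance, nothing is set aside for missing outcomes.

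**2. Scores missing independently at rate m.** The share of patients with complete data is (1 − m)^k, with k = 9 × 3 = 27 for three visits or 9 × 2 = 18 for baseline and week 4. Power is that of the plan's own kind of calculation, a two-group comparison at 0.75 SD with two-sided 5%: Φ(0.75·√(n/2) − 1.96), with n per arm. It is not the power of the multivariate test.

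| m | k = 27: share complete | of 70 | power | k = 18: share complete | of 70 | power |
|---|---|---|---|---|---|---|
| 0% | 1.00 | 70 | 0.88 | 1.00 | 70 | 0.88 |
| 1% | 0.762 | 53 | 0.78 | 0.835 | 58 | 0.82 |
| 2% | 0.580 | 41 | 0.67 | 0.695 | 49 | 0.74 |
| 3% | 0.439 | 31 | 0.55 | 0.578 | 40 | 0.67 |

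The rate that brings 70 down to 56 solves (1 − m)^k = 0.80. For k = 27, m = 1 − 0.80^(1/27) = 0.8%. For k = 18, m = 1 − 0.80^(1/18) = 1.2%.

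**3. Whole visits missed, nothing else.** Assume 10% missing at week 4 and 20% at follow-up. If everyone who misses week 4 also misses follow-up, the loss is 20%, leaving 56. If the two are independent, the loss is 1 − 0.9 × 0.8 = 28%, leaving about 50. With baseline and week 4 only, the loss is 10%, leaving 63.

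**4. Functional MANOVA.** Two scores, the neurological composite and the dependence scale, over three visits make six. At m = 1%, 2% or 3%, 70 × (1 − m)⁶ = 66, 62 or 58 patients remain. The functional minimum in the article is 34.

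**The case against.** The strongest reply is that a journal article may leave missing-data handling to the full protocol or analysis plan, and that imputing before the MANOVA is compatible with every sentence printed. That stands, and silence alone would not be a finding. But the article does more than stay silent: it fixes a method that, used as stated, excludes incomplete patients, and beside it states a principle that covers everyone randomized.

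A second reply is that intention to treat is set here against per-protocol and compliance analyses, so it chiefly means analysis by allocated arm. MANOVA allows that. This too stands in part, and it is why the two statements fit poorly but do not flatly contradict each other.

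A third reply concerns the amount missing. Severe aphasia and confusion are exclusions, and patients must be able to take the neuropsychological assessment, so baseline may be nearly complete. If it were fully complete, three visits would leave 18 scores at risk, which is the right half of the table. Two visits would leave nine, and 70 × (1 − m)⁹ = 64, 58 or 53 patients at 1%, 2% or 3%. Missing scores also cluster within patients and visits, which lowers the loss. Discharge is not dropout, and nothing in the article says that discharged patients go untested. All of this stands. The independence figures are a pessimistic end, not a forecast.

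A reader might infer that any single missed test removes the patient. The article does not support this: tests within a domain are averaged, and the rule for a partly missing domain is not given. It is the missing domain score that counts.

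**Conclusion.** The point holds in a limited form. Run as stated and without imputation, the cognitive MANOVA analyses only patients with every domain score at every visit in the time factor. That fits poorly with the stated intention-to-treat principle and with a sample size that allows nothing for dropout.

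The size depends on unknown rates. Under independent missingness, about 1% per domain score is enough to reach the plan's minimum of 56: 0.8% over three visits, 1.2% over two. Under visit-level loss at the assumed rates, 50 to 56 patients remain over three visits. Three visits is the natural reading of the time factor. Baseline and week 4 is also possible, because the control arm starts CPAP afterwards. The functional analysis is little affected.

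Two stronger conclusions may tempt a reader. The first is that the plan cannot deliver an intention-to-treat analysis. It can, if values are imputed or a different model is fitted, and the article rules out neither. The second is that nine domains are too many and should be replaced by one mean score. The documents do not support this: they give no correlations between domains, and the Background reports a slight CPAP benefit in attention only, which an average over nine domains would dilute.

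**What to change.** Make the primary analysis a linear mixed model for repeated measures with arm × visit, using all available scores of all randomized patients. SPSS has this as MIXED. For cognition, keep the nine domains, for example with domain as a further repeated factor and a joint test of the nine arm differences at week 4. Read the arm contrast at week 4, since after that both arms may be on CPAP. Alternatively, keep the MANOVA and state that multiple imputation precedes it. In either case, list the levels of the time factor and say how a partly missing domain is scored. Keep the Hochberg procedure across cognition and function, and report the complete-case MANOVA as a sensitivity analysis.

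The cost is wording and somewhat more modelling work; data collection does not change. The covariance structure must be chosen in advance. An unstructured matrix for 27 scores has 27 × 28 / 2 = 378 parameters, too many for 70 patients, so a structured form is needed. Both the mixed model and standard multiple imputation rest on a missing-at-random assumption, which should be stated.

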### Secondary outcomes

Secondary outcome measures of the TOROS study are sleepiness (Stanford Sleepiness Scale), fatigue (Checklist Individual Strength), mood (Hospital Anxiety and Depression Scale), and subjective sleep quality (Sleep Quality Scale) [31-34]. A trained psychological assistant administers these measures after the neuropsychological assessment. The Utrecht Scale for Evaluation of Rehabilitation – Participation [35] is used to evaluate work, leisure and social activities at six months and one year after the inclusion. The patients complete this questionnaire at home.

Objective measurements of sleep are made using standardized pulse oximetry (WristOx®; Nonin Medical, Plymouth, USA) and ambulatory overnight cardiorespiratory polygraphy (Embletta®; Embla, Ottowa, Canada). The ODI (mean number of oxygen desaturations of ≥3% per hour) is calculated from the pulse oximetry data using automated analysis. Trained staff manually scores the polygraph recordings. Apnea is defined as a reduction of airflow of ≥90% for at least 10 seconds and hypopnea is defined as a reduction of airflow of ≥50% for at least 10 seconds followed by an oxygen desaturation of ≥3%. The AHI is defined as the mean number of apneas and hypopneas per hour in bed. The change of AHI measured by polygraphy and treatment compliance are used as moderating variables in the RCT.

A self-report questionnaire is administered to identify OSA symptoms (e.g., snoring, daytime sleepiness, morning headaches). Socio-demographic and clinical characteristics such as age, sex, education, body mass index (BMI), medication use and life style variables (e.g., smoking) are obtained from medical records.

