### Sample size

We conducted two separate power analyses for the RCT; one for the functional outcome and one for the cognitive outcome. The power calculation for the functional outcome is based on two previous studies [18,19]. These studies found large effects of CPAP treatment on functional outcome measures in stroke patients. To detect at least one standard deviation (large effect) on functional outcome with 90% power and an alpha of 0.05 (one-tailed), a minimum of 34 patients (17 per arm) is required.

No reliable information on the expected effect of CPAP treatment on cognitive measures is available. Therefore, an effect size of 0.75 standard deviation was used to estimate the necessary sample size. Taken the same alpha level and 80% power, a minimum of 56 patients (28 per arm) needs to be included in the RCT. The compliance in this study is expected to be relatively high (around 67%) due to the relatively short duration of the experimental treatment phase and the assistance of a specially trained staff. Taking the compliance rate into account, a total of 70 patients will be the target sample size for the RCT.

For the supplementary case–control study, we set the sample size at 70 OSA patients and 70 patients without OSA, which allows detection of a medium size effect (0.5 standard deviation) with 90% power, and p-value set at 0.5.

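### In the OSA versus non-OSA comparison, covariates are chosen by whether a baseline difference is observed, so moderate confounders can go unadjusted, mainly for the functional scales and for BMI and smoking

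*Protocol article*

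**What the plan says.** Under Patient sample and procedures, the groups are formed by sleep testing: "Patients with an AHI of 15 or higher on polygraphy are diagnosed with OSA". Patients with a normal ODI or a lower AHI are the non-OSA group. Group membership is therefore not randomised.

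Under Statistical analyses, "OSA patients will be compared with the control group of non-OSA patients on primary and secondary outcome measures using a MANOVA". No covariates are listed for this model. The section's general rule is: "If group differences are observed at baseline on one or more background variables, those variables will be included as covariates in all further analyses". It gives no test or cut-off for what counts as observed. The general significance level appears shortly before it: "Statistical significance will be set at a p-value of 0.05 or less". The follow-up comparison of participation (USER-P) between groups is a two-sample t-test.

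Under Secondary outcomes, the recorded background data are "Socio-demographic and clinical characteristics such as age, sex, education, body mass index (BMI), medication use and life style variables (e.g., smoking" and similar items. None is made a fixed covariate.

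Under Primary outcomes, the cognitive test scores are converted to z-scores corrected for demographics, with no condition attached. No such correction is stated for the neurological or functional-dependence scales.

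The Background describes this comparison as exploring an association, with the hypothesis that patients with OSA do worse.

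**The concern.** In the randomised comparison, baseline differences arise by chance, and a rule of this kind costs mainly efficiency. In a comparison of naturally occurring groups, a difference in a background variable may be systematic. What then matters is whether the variable relates both to OSA and to the outcome.

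The rule looks only at the first relation, and only through what one sample of 140 happens to show. A genuine confounder of moderate size can be left out because its difference was not noticed. A variable unrelated to outcome, or one that may be a consequence of OSA, can be let in because its difference was noticed.

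At stake is the OSA versus non-OSA estimate for function and, in part, for cognition. If the omitted variables are commoner in OSA and worsen outcome, the error runs in the direction of the stated hypothesis. The USER-P comparison has a further problem: a two-sample t-test cannot carry the covariates that the rule would call for.

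**Working it through.** **Inputs from the protocol article.** 70 per group ("we set the sample size at 70 OSA patients and 70 patients without OSA"); target difference 0.5 SD; significance level 0.05; the covariate rule quoted above.

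**The plan's own figure.** Normal approximation: n per group = 2(z_α + z_β)² / 0.5².
- One-sided 0.05, 90% power: 2(1.645 + 1.282)² / 0.25 = 68.5, so 69 (t-test version 69.2, so 70). Power at 70 is about 0.90.
- Two-sided 0.05: 2(1.960 + 1.282)² / 0.25 = 84.1, so 85. Power at 70 is 0.84.

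So 70 per group reproduces with a one-sided 0.05 test. The article states one-sidedness only for the randomised comparison ("with 90% power and an alpha of 0.05 (one-tailed"). For this comparison it prints "which allows detection of a medium size effect (0.5 standard deviation) with 90% power, and p-value set at 0.5", which conflicts with the 0.05 elsewhere and is a separate point. Because sidedness is unclear here, both versions are shown below.

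**How often the rule picks up a confounder.** Assumption: observed means p ≤ 0.05 in a two-sided t-test. The noncentrality is d × √(70/2) = 5.92d.

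| True difference d | 5.92d | Probability of selection |
|---|---|---|
| 0.2 SD | 1.18 | 0.217 |
| 0.3 SD | 1.77 | 0.422 |
| 0.4 SD | 2.37 | 0.652 |
| 0.8 SD | 4.73 | 0.997 |

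A 0.3 SD confounder is therefore left out in about 58% of studies. Large imbalances are caught.

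**What that does to the OSA estimate.** This was simulated with 70 v 70, no true OSA effect, one continuous outcome in place of the MANOVA, and independent normal confounders that all worsen outcome and are all higher in OSA. The strengths are assumptions; the documents give none.

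With no adjustment, the bias is (number of confounders) × (difference) × (slope). For one confounder at 0.3 SD and slope 0.3 that is 0.09 SD; for three it is 0.27 SD. The simulation returned 0.09 and 0.269. Under the rule, less bias remains:

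| Confounders | Difference, slope | Bias left by rule | False positives, two-sided | One-sided |
|---|---|---|---|---|
| 1 | 0.3 SD, 0.3 | 0.03 SD | 5.3% | 7.1% |
| 1 | 0.3 SD, 0.5 | 0.05 SD | 5.8% | 8.7% |
| 3 | 0.2 SD, 0.2 | 0.06 SD | 6.4% | 10.3% |
| 3 | 0.3 SD, 0.3 | 0.10 SD | 8.3% | 13.8% |
| 4 | 0.3 SD, 0.3 | 0.13 SD | 11.9% | 19.0% |
| 5 | 0.3 SD, 0.3 | 0.16 SD | 16.3% | 25.5% |

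With the same variables always included, the bias is about 0 and the false-positive rate about 5% throughout.

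**Sensitivity to the assumptions (two-sided).**
- Four confounders as above, one acting in the opposite direction: about 6%. Two reversed: about 5%, with bias about 0.
- Four confounders correlated at 0.3, slope 0.2: 5.3%, bias 0.04 SD.
- Observed read as a standardized difference above 0.2: four confounders give 5.0% and 0.03 SD; five give 5.6% and 0.04 SD.

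**The case against.** The strongest reply has four parts.

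**Demographics in cognition are already handled.** This stands. The correction of the cognitive z-scores does not depend on any baseline difference. A reader might infer that every confounder of both primary outcomes hangs on the rule; the article does not support that. Which demographics enter the z-scores is not stated, but BMI and smoking are not demographic variables, and the functional scales have no stated correction.

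**The 0.05 cut-off is supplied, not quoted.** This also stands. The rule follows a sentence about descriptive statistics, and a looser reading of observed removes most of the inflation. It remains true that the rule fixes no cut-off and ignores outcome on any reading.

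**The larger figures depend on stacked assumptions.** Several moderate, independent confounders must all push the same way. A reader might take 0.16 SD, about a third of the 0.5 SD target (0.16/0.5 = 0.32), as the expected bias, or conclude that the plan favours a false confirmation of its hypothesis. The documents give no imbalances, slopes or directions, so neither inference is supported. The figures show what could happen.

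**The comparison is supplementary and exploratory.** True, and the randomised comparison is not affected by this point. But this part has its own hypothesis, sample size and multiplicity procedure, so its estimate will be read as a result.

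A reader might also treat the lack of matching as established. The article states none, but a condensed article may leave the selection of controls to the full protocol. Nor is this a complaint that a covariate list is missing: the rule itself is printed, and it is the rule that is poorly suited to a non-randomised contrast.

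**Conclusion.** The point holds, within limits. In the OSA versus non-OSA comparison, the plan selects covariates by observed imbalance and disregards their relation to outcome. Reading observed as p ≤ 0.05, moderate confounders are adjusted for in only about a fifth to two thirds of studies. The consequence is small for a single confounder (about 0.04 SD; 5–6% two-sided). It becomes material only with several confounders in the same direction (about 0.06–0.16 SD with three to five; 6–16% two-sided, and more if testing is one-sided). It largely vanishes with mixed directions or a cut-off near 0.2 SD.

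These sizes rest on assumed confounder strengths, on independence, and on a single outcome in place of the MANOVA with the Hochberg step. The point applies fully to the functional scales, to non-demographic confounders of cognition, and to the unadjusted USER-P comparison. The change should be made, but the point does not undermine the trial's main question.

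**What to change.** For the OSA versus non-OSA comparison only, replace the observed-difference rule with a confounder set fixed in advance on subject-matter grounds and entered whatever the baseline differences. Draw it from data already recorded or available from the medical record, for example age, sex, education, BMI, smoking, stroke subtype and time since stroke. Decide beforehand, and give the reason, whether a variable such as medication use is a confounder or a possible consequence of OSA; the baseline table should not settle that.

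Use the same adjusted model (ANCOVA) for the between-group USER-P comparison in place of the two-sample t-test. Show the unadjusted result alongside, and word conclusions as association.

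The cost is a sentence or two in the plan and no new data. Seven single-degree covariates reduce the error degrees of freedom from 140 − 2 = 138 to 131. The interval widens slightly if a listed variable is strongly related to OSA but not to outcome.
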